# A pragmatic randomized controlled trial to evaluate the efficacy and safety of an oral short-course regimen including bedaquiline for the treatment of patients with multidrug-resistant tuberculosis in China: study protocol for PROSPECT

**DOI:** 10.1186/s13063-024-07946-9

**Published:** 2024-04-01

**Keywords:** Tuberculosis, Bedaquiline, China, Oral Short-course regimen

## Abstract

**Introduction:**

The lack of safe, effective, and simple short-course regimens (SCRs) for multidrug-resistant/rifampicin-resistant tuberculosis (MDR/RR-TB) treatment has significantly impeded TB control efforts in China.

**Methods:**

This phase 4, randomized, open-label, controlled, non-inferiority trial aims to assess the efficacy and safety of a 9-month all-oral SCR containing bedaquiline (BDQ) *versus* an all-oral SCR without BDQ for adult MDR-TB patients (18–65 years) in China. The trial design mainly mirrors that of the “Evaluation of a Standardized Treatment Regimen of Anti-Tuberculosis Drugs for Patients with MDR-TB” (STREAM) stage 2 study, while also incorporating programmatic data from South Africa and the 2019 consensus recommendations of Chinese MDR/RR-TB treatment experts. Experimental arm participants will receive a modified STREAM regimen C that replaces three group C drugs, ethambutol (EMB), pyrazinamide (PZA), and prothionamide (PTO), with two group B drugs, linezolid (LZD) and cycloserine (CS), while omitting high-dose isoniazid (INH) for confirmed INH-resistant cases. BDQ duration will be extended from 6 to 9 months for participants with *Mycobacterium tuberculosis*-positive sputum cultures at week 16. The control arm will receive a modified STREAM regimen B without high-dose INH and injectable kanamycin (KM) that incorporates experimental arm LZD and CS dosages, treatment durations, and administration methods. LZD (600 mg) will be given daily for ≥ 24 weeks as guided by observed benefits and harm. The *primary outcome* measures the proportion of participants with favorable treatment outcomes at treatment completion (week 40), while the same measurement taken at 48 weeks post-treatment completion is the *secondary outcome*. Assuming an *α* = 0.025 significance level (one-sided test), 80% power, 15% non-inferiority margin, and 10% lost to follow-up rate, each arm requires 106 participants (212 total) to demonstrate non-inferiority.

**Discussion:**

PROSPECT aims to assess the safety and efficacy of a BDQ-containing SCR MDR-TB treatment at seventeen sites across China, while also providing high-quality data to guide SCRs administration under the direction of the China National Tuberculosis Program for MDR-TB. Additionally, PROSPECT will explore the potential benefits of extending the administration of the 9-month BDQ-containing SCR for participants without sputum conversion by week 16.

**Trial registration:**

ClinicalTrials.gov NCT05306223. Prospectively registered on 16 March 2022 at https://clinicaltrials.gov/ct2/show/NCT05306223?term=NCT05306223&draw=1&rank=1 {2}.

**Supplementary Information:**

The online version contains supplementary material available at 10.1186/s13063-024-07946-9.

## Introduction

### Background and rationale {6a}

Multidrug-resistant and rifampicin-resistant tuberculosis (MDR/RR-TB) poses a significant challenge to global public health. Regrettably, between 2018 and 2021 a mere 648,953 patients across the globe started second-line treatment for this serious condition, a number amounting to just 43% of the 1.5 million 5-year target for 2018–2022 that was established during the United Nations high-level meeting on TB in 2018 [1]. To address this issue, there is an urgent need for research and innovation, one of the three pillars of the End TB Strategy [2], to facilitate the development of shorter, safer, and efficacious MDR/RR-TB treatments. Prior to 2016, second-line anti-TB injectable drugs and oral drugs are administered to MDR/RR-TB patients for 6 to 8 months as an integral part of a 20-month treatment regimen. However, despite ongoing efforts, treatment success rates for MDR/RR-TB patients have remained disappointingly low. Moreover, patients must grapple with a substantial pill burden, significant adverse events, and other issues that have led to unsatisfactory treatment compliance [3]. Tragically, mortality rates associated with this relentless disease have been reported to approach 15% [4]. Since its introduction in 2010, the use of the shorter-course “Bangladesh regimen” [5] has been observed to achieve a high relapse-free cure rate, prompting the WHO to recommend further exploration of such regimens under operational conditions [6–10]. In 2016, the WHO issued conditional recommendations to guide the use of a standardized shorter-course MDR/RR-TB treatment regimen or a modified version of it based on local treatment experiences, as informed by results of observational studies conducted in various Asian and African countries [3].

In 2019, the WHO published consolidated drug-resistant TB (DR-TB) treatment guidelines that included key changes made to MDR/RR-TB treatment protocols [11]. The revised guidance introduces a priority ranking-based classification scheme for available anti-TB treatment drugs. In this scheme, BDQ is recommended and prioritized for use as a core drug (Group A) in the longer-course MDR/RR-TB treatment regimen, with LZD also recommended for inclusion as a core drug. A third Group A drug, such as levofloxacin (LFX) or moxifloxacin (MFX), and at least one Group B drug, such as clofazimine (CFZ), cycloserine (CS), or terizidone (TZD), are recommended for use in the longer-course MDR/RR-TB treatment regimen to ensure that at least four potentially effective TB agents are administered at treatment initiation. As an additional modification, kanamycin (KM) and capreomycin (CM) were deprioritized as components of MDR/RR-TB treatment regimens [11]. Meanwhile, the “Chinese expert consensus of MDR-TB and RR-TB treatment” guidelines issued in October 2019 recommend the reprioritization of certain drugs, as based on WHO 2019 guidance recommending the incorporation of BDQ in both long-course regimens (LCRs) and SCRs used to treat MDR-TB patients [12].

In December 2019, the WHO issued a Rapid Communication [13] advocating the adoption of a shorter-course, all-oral, BDQ-containing regimen for MDR/RR-TB patients to replace the standard shorter-course injectables-based regimen. At the same time, the results of a study conducted in South Africa [14, 15] prompted the WHO to recommend transitioning away from the standard regimen. These revisions are incorporated within the current WHO consolidated guidelines issued in 2020 [16] along with guidelines for administering a shorter-course (9–12-month) all-oral BDQ-containing regimen for treatment of eligible MDR/RR-TB cases lacking both resistance to fluoroquinolones (FQs) and prior treatment histories of greater than 1-month’s duration to second-line TB drugs included in the shorter-course, all-oral regimen.

As access to newer and repurposed TB drugs increases, Chinese researchers are increasingly focused on developing shortened regimens with lower toxicity and non-inferior or better efficacy that eliminate the need for injectables. The “Pragmatic Randomized Controlled Trial to Evaluate the Efficacy and Safety of an Oral Short-course Regimen Including BDQ for the Treatment of Patients with Multidrug-resistant Tuberculosis in China” (PROSPECT) was designed to compare the safety and efficacy of a modified 40-week all-oral, BDQ-containing SCR MDR-TB treatment to corresponding performance indicators of a 40-week all-oral SCR without BDQ. The design of the new MDR-TB treatment regimen, which primarily incorporates key drugs of regimens B and C evaluated in the STREAM stage 2 study [6], was further modified based on recommendations of experts, as indicated in the 2019 “Chinese expert consensus of MDR-TB and RR-TB treatment” guidelines^12]^. For the experimental arm treatment, modifications were made to the original STREAM regimen C. In accordance with principles governing LCR design, the three group C drugs EMB, PZA, and PTO were replaced with the two group B drugs LZD and CS and high-dose INH, while BDQ treatment duration was increased from 6 to 9 months for participants who were still sputum culture-positive for *MTB* at week 16. For the control arm, an 18–20-month injectables-based regimen, the recommended standard of care (SOC) MDR-TB treatment since 2016 [17], was replaced with the WHO-endorsed shorter-course 9–11-month injectables-based regimen in 2018 [18]. However, modified standardized shorter-course MDR-TB regimens are currently being developed for Chinese MDR-TB patients. For example, the PROSPECT control arm receives a modified treatment, whereby KM is replaced with LZD to remove the need for injectables that are no longer recommended by the WHO. Additionally, high-dose INH was removed, due to concerns stemming from (1) the high *KatG* mutation rate observed in INH-resistant *MTB* isolates obtained from patients in China, which implies that most Chinese TB cases with high-level INH resistance will not benefit from high-dose INH; (2) the small proportion of Chinese MDR-TB patients who carry a certain *ihnA* mutation who may benefit from high-dose INH treatment should be excluded, due to PTO cross-resistance conferred by this mutation; and (3) the safety profile of high-dose INH when used to treat Chinese patients has not been verified. In summary, the PROSPECT experimental arm modifications were made based on the original STREAM regimen C and the control arm regimen was modified based on the regimen B used in the STREAM study [6], by removing high-dose INH and injectable KM and intensified by incorporating LZD and CS.

The original PROSPECT protocol was submitted to regulatory officials on Mar 26, 2020. Two versions of the protocol were subsequently amended on Mar 9, 2021, and Dec 8, 2021, as requested by the China Center for Drug Evaluation (CDE). As a post-marketing approval commitment study, the results of PROSPECT are expected to provide updated evidence-based guidance for improving MDR-TB treatment practices in China.

## Objectives {7}

### Primary objectives

To evaluate the performance of an oral BDQ-containing SCR at treatment completion by comparing its efficacy to that of an oral SCR without BDQ in participants with pulmonary MDR-TB in China.

### Secondary objectives

To compare favorable treatment outcomes of an all-oral BDQ-containing SCR versus those of an all-oral SCR without BDQ at 48 weeks post-treatment completion in participants with pulmonary MDR-TB in China.To evaluate efficacy based on treatment success of an all-oral BDQ-containing SCR versus an all-oral SCR without BDQ at treatment completion in participants with pulmonary MDR-TB in China.To evaluate the safety of an all-oral BDQ-containing SCR versus that of an all-oral SCR without BDQ in participants with pulmonary MDR-TB in China.To evaluate modified favorable treatment outcomes associated with the administration of an all-oral BDQ-containing SCR versus outcomes of an all-oral SCR without BDQ at treatment completion and at 48 weeks post-treatment completion in participants with pulmonary MDR-TB in China.To evaluate TB relapse and re-infection rates during the post-treatment follow-up phase in participants with pulmonary MDR-TB in China.To evaluate rates of emerging resistance to BDQ and other anti-TB drugs incorporated within the all-oral SCR with and without BDQ regimen used to treat participants with pulmonary MDR-TB in China.

## Trial design {8}

This is an open-label, parallel-group, randomized, controlled, multicenter, interventional, pragmatic, phase 4, clinical study that assesses non-inferiority. The study aims to assess the efficacy and safety of an oral BDQ-containing SCR as compared to corresponding performance indicators of an oral SCR without BDQ. Our goal is to enroll a total of 212 participants (106 participants/regimen) aged 18 to 65 years with microbiologically confirmed pulmonary MDR-TB. The study will be implemented within the framework of the China Tuberculosis Clinical Trial Consortium (CTCTC) network [19].

The PROSPECT study process consists of a screening phase of up to 8 weeks, a study treatment phase of 40 weeks, and a 48-week follow-up phase occurring after treatment completion. Monitoring of all recruited participants will be conducted for 88 weeks post-randomization after completion of the screening phase. A diagram outlining the study design is provided in Fig. 1.

**Fig. 1 Fig1:**
[figure not shown]
Schematic overview of the study design. BDQ, bedaquiline; CFZ, clofazimine; CS, cycloserine; LFX, levofloxacin; LZD, linezolid; PTO, prothionamide; PZA, pyrazinamide. ^a^If a participant is still sputum culture-positive for *Mycobacterium tuberculosis* by week 16, BDQ treatment will be extended from 24 to 40 weeks

Assessments are scheduled at regular intervals according to the type of drug administered (Table 1), which aligns with local SOC practices. Efficacy assessments conducted at all sites will include sputum smears, sputum cultures performed using the Mycobacteria Growth Indicator Tube (MGIT) 960 system, drug susceptibility testing (DST) in cases with positive sputum cultures, and genotyping/fingerprinting of *MTB* isolates obtained from relapse or reinfection cases.

**Table 1 Tab1:** Assessment schedule for patients recruited{13}

	**Study period**																
**Phase**	**Screening**	**Study Treatment**												**Follow-up**			
**Timepoint**	**W-8 to D-1**	**D1/BSL**	**W2**	**W4**	**W8**	**W12**	**W16**	**W20**	**W24**	**W28**	**W32**	**W36**	**W40**	**W52**	**W64**	**W76**	**W88**
**Enrolment:**																	
Screening																	
Informed consent	X																
Inclusion/exclusion criteria	X																
Chest CT	X					X			X			X					
Medical history and demographics	X																
Pregnancy test	X	X				X							X				
HIV test	X																
Symptoms/weight	X	X	X	X	X	X	X	X	X	X	X	X	X	X	X	X	X
Physical examination	X	X	X	X	X	X	X	X	X	X	X	X	X	X	X	X	X
Randomization		X															
**Interventions:**																	
Dispense/administer allocated TB treatment		X	X	X	X	X	X	X	X	X	X	X	X				
**Assessments:**																	
Study treatment adherence assessment			X	X	X	X	X	X	X	X	X	X	X	X			
Efficacy and safety evaluations																	
Sputum smear	X	X	X	X	X	X	X	X	X	X	X	X	X	X	X	X	X
Sputum culture	X	X	X	X	X	X	X	X	X	X	X	X	X	X	X	X	X
Molecular DST	X																
Collect strains for phenotypic DST (only in case of positive sputum culture)	X	X	X	X	X	X	X	X	X	X	X	X	X	X	X	X	X
Visual acuity testing	X	X	X	X	X	X	X	X	X	X	X	X	X				
Urinalysis	X	X	X	X	X	X	X	X	X	X	X	X	X				
Hematology	X	X	X	X	X	X	X	X	X	X	X	X	X				
Clinical chemistry^a^	X	X	X	X	X	X	X	X	X	X	X	X	X				
Hepatitis B and C testing		X															
TSH^b^	X	X				X			X								
ECG^c^	X	X	X	X	X	X	X	X	X	X	X	X	X				
Ongoing participant review																	
Concomitant therapy	X	X	X	X	X	X	X	X	X	X	X	X	X	X	X	X	X
AEs	X	X	X	X	X	X	X	X	X	X	X	X	X	X	X	X	X

X indicates assessments required at particular visits. *BSL* Baseline, *CT* Computerized tomography, *D* Day, *W* Week

^a^Will include liver and kidney function tests and electrolytes and blood glucose measurement

^b^Will be conducted at screening for all subjects; subsequent TSH testing will be conducted only if participant is receiving PTO

^c^ECG measurement should be continued during follow-up for patients whose bedaquiline course is extended to 40 weeks duration, and as clinically indicated to follow patients with increases in QTcF at the end of treatment until resolution

Safety evaluations will include regular physical examinations, monitoring of adverse events (AEs), visual acuity testing, urinalysis testing, electrocardiograms (ECGs), and routine blood testing to assess levels of hematological, chemical, and hepatitis B and C markers and levels of thyroid-stimulating hormone (TSH) for PTO-treated participants. In addition, hepatitis B and C status will be checked at baseline.

## Methods: participants, interventions, and outcomes

### Study setting {9}

The trial is sponsored by the Innovation Alliance on Tuberculosis Diagnosis and Treatment, Beijing (IATB) and conducted at Beijing Chest Hospital, Capital Medical University, and 16 other TB-specialized hospitals nationwide that are equipped to provide trial participants with both ambulatory and hospital-based care. Site details are available on the ClinicalTrials website (https://register.clinicaltrials.gov/prs/app/template/Home.vm?uid=U000369X&ts=39&sid=S000BTRA&cx=-t8d5e0.). The study protocol was drafted in accordance with the Standard Protocol Items: Recommendations for Interventional Trial guidelines (SPIRIT) [20].

### Eligibility criteria {10}

#### Inclusion criteria

A prospective participant must satisfy all of the following criteria to be enrolled in the study:

**Table Taba:** 

1	Is willing and able to provide written informed consent (signed or witnessed consent if the participant is illiterate) to participate in study-related treatment and follow-up care activities
2	Tests positive for *MTB* via sputum culture during the screening period
3	Has microbiologically confirmed RIF resistance as determined via GeneXpert and *katG* mutation-induced resistance to INH, as revealed via molecular DST
4	Has chest imaging findings supporting a diagnosis of pulmonary TB
5	Is a man or woman aged 18 to 65 years
6	Agrees to use effective contraception during the 40-week study treatment phase; a non-vasectomized male participant must agree to use condoms during the 40-week study treatment phase
7	Has normal serum K^+^, Mg^2+^, and corrected Ca^2+^ levels at screening
8	Is willing to undergo HIV testing
9	Resides in close proximity to the study site and is able to remain under observation for the duration of the study

#### Exclusion criteria

Any potential participant who meets any of the following criteria will be excluded from participating in the study:

**Table Tabb:** 

1	Is infected with a strain of *MTB* with molecular DST-confirmed resistance to FQs, previously tested positive via phenotypic DST for resistance to any drug in the regimen or tested positive for low-level INH resistance that was either confirmed by phenotypic DST or through molecular detection of the *inhA* mutation
2	Has received prior BDQ treatment
3	Had prior exposure to at least one second-line drug in the regimen for at least 4 weeks
4	Is known to be pregnant, is planning to become pregnant, or is breastfeeding
5	Is unable or unwilling to comply with study treatment protocols or follow-up schedules
6	Has a grade three or grade four laboratory abnormality based on Division of AIDS (DAIDS) grading, as confirmed by a clinical expert
7	Has a blood ALT/AST ratio that is greater than three times the upper limit of normal (ULN) or a total blood bilirubin level greater than two times the ULN (participants with Gilbert’s disease will not be excluded as long as the total blood bilirubin level is < 2 × ULN); creatinine clearance of < 30 mL/min; blood hemoglobin level of ≤ 7.0 g/dL; blood platelet count of < 50 × 10^9^/L at screening
8	Is taking any medication contraindicated with drugs in the regimen
9	Has a known allergy or intolerance to BDQ or other drugs in the regimen
10	Is currently taking part in another study of a medicinal product
11	Has a QTcF of ≥ 450 ms at screening
12	Has a history of Torsade de Pointes or a history of cardiac risk factors for Torsade de Pointes, including a personal or family history of long QT syndrome, ongoing hypothyroidism, heart failure, or bradycardia (as defined by a sinus rate of < 50 bpm)
13	Has a history of syncopal episodes (i.e., cardiac syncope not including syncope due to vasovagal or epileptic causes) or symptomatic or asymptomatic arrhythmias
14	Has concomitant severe disease affecting cardiovascular, hepatic, renal, neurological, hematopoietic, or other systems or concomitant neoplastic disease(s)
15	Has uncontrolled diabetes mellitus
16	Has a concomitant mental disorder and, in the judgment of the investigator, is not fit for the study or unlikely to complete the full course of the study
17	Is HIV-positive
18	Is critically ill and, in the judgment of the investigator, is not fit for inclusion in the study or is unlikely to complete the full course of the study
19	Is infected with a strain of nontuberculous mycobacteria
20	Has isolated extrapulmonary disease
21	Has extrapulmonary disease that is miliary in nature or extrapulmonary disease involving the central nervous system and/or the skeletal system

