#### Criteria for discontinuing or modifying allocated interventions {11b}

A participant’s study intervention must be discontinued if:The participant withdraws consent to receive the study intervention.The investigator believes that for safety or tolerability reasons it is in the best interest of the participant to discontinue the study intervention. Individual drug substitutions within the study intervention regimen may be considered if clinically indicated at the discretion of the investigator. Administration of single-drug substitutions will not be viewed as an unfavorable treatment outcome criterion if limited to substitutions of non-group A drugs (except DLM) as per the 2020 WHO MDR-TB treatment guidelines.The participant becomes pregnant.Unacceptable toxicity.The patient experiences:Aminotransferase elevations with total bilirubin elevations to levels of ≥ twofold the ULNAminotransferase elevations to levels that are ≥ eightfold greater than the ULNAminotransferase elevations to levels that are ≥ fivefold greater than the ULN and persist for more than 2 weeks.If the patient experiences a QTcF interval > 500 ms (as confirmed by repeat ECG) and/or clinically significant ventricular arrhythmia.Noncompliance with study drug administration.Any participant not meeting eligibility criteria as specified in the “Eligibility criteria” section.

A participant will be withdrawn from the study for any of the following reasons:If phenotypic DST results from a screening sample become available post-baseline confirming resistance at the start of the study to any of the drugs in the assigned regimen except BDQ, in which case the patient will be treated according to local treatment protocols after withdrawal from the study.Lost to follow-up.Withdrawal of consent.Death.

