### Plans for communicating important protocol amendments to relevant parties (e.g., trial participants, ethical committees) {25}

All protocol amendments must be issued by the sponsor/designee and signed and dated by the investigator. Protocol amendments must not be implemented without prior approval of the Research Ethics Committee (REC) and/or IRB or when the relevant competent authority has raised concerns that may lead to non-acceptance, except when such amendments are necessary to eliminate immediate hazards to participants. In such exceptional cases, the amendment must be promptly submitted to the REC/IRB and relevant competent authority. Documentation of amendment approval by the investigator and REC/IRB must be provided to the sponsor/designee. For changes limited to logistical or administrative aspects of the study, notification to the REC/IRB (where required) suffices. Both the original protocol and any subsequent amendments must be submitted to the appropriate regulatory authorities, and the study cannot commence until all local regulatory prerequisites are met.

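### Exclusion criterion 7 sets its liver-enzyme limit on the ALT/AST ratio, which has no defined ULN, instead of on the ALT or AST level

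*Protocol article*

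**What the plan says.** Exclusion criterion 7 (Eligibility criteria {10}) excludes a patient who "Has a blood ALT/AST ratio that is greater than three times the upper limit of normal (ULN". The next part of the same item excludes "a total blood bilirubin level greater than two times the ULN".

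Two other exclusion items bear on the liver:
- Item 6: "Has a grade three or grade four laboratory abnormality based on Division of AIDS (DAIDS) grading, as confirmed by a clinical expert".
- Item 14: "Has concomitant severe disease affecting cardiovascular, hepatic, renal, neurological, hematopoietic, or other systems".

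Section {11b}, on discontinuing the allocated intervention, has three hepatic stopping rules: an aminotransferase rise with bilirubin at or above twice the ULN; aminotransferases at or above eight times the ULN; and aminotransferases at least "fivefold greater than the ULN and persist for more than 2 weeks". The same list also requires the intervention to be stopped for "Any participant not meeting eligibility criteria as specified in the" eligibility section.

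The abbreviation list spells out ULN and adds nothing more. No reference range for an ALT/AST ratio appears anywhere.

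**The concern.** An upper limit of normal belongs to a measured level. Three times the ULN is a natural limit for ALT or for AST, but it has no defined meaning for the quotient of the two. A quotient also loses the information a liver-safety limit needs: when both enzymes rise together, numerator and denominator grow alike and the ratio stays put. Read literally, the rule cannot tell such a patient from one with normal enzymes.

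The item decides eligibility at 17 sites for regimens whose own stopping rules treat raised aminotransferases as a reason to stop. It still matters once enrolment closes, because {11b} makes failure to meet the eligibility criteria a reason to stop the intervention, and Outcomes {12} counts treatment discontinuation as unfavorable. How item 7 is read can therefore decide how an individual participant is treated and classified. No bias between arms and no effect on sample size or power is claimed.

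**Working it through.** The plan gives no statistical figure to reproduce. The check sets the hepatic limits side by side and then tests what a ratio can detect.

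**1. The limits compared**

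| Place | Quantity limited | Limit |
|---|---|---|
| Exclusion 7, enzymes | ALT/AST ratio | > 3 × ULN |
| Exclusion 7, bilirubin | level | > 2 × ULN |
| {11b}, combined rule | bilirubin level, with an aminotransferase rise (no multiple given) | ≥ 2 × ULN |
| {11b}, single rule | aminotransferase level | ≥ 8 × ULN |
| {11b}, persistent rule | aminotransferase level | ≥ 5 × ULN for more than 2 weeks |

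Only the enzyme part of exclusion 7 limits a ratio.

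**2. Parallel rises**

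Let both enzymes be at k times their own ULN. Then

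ratio = (k × ULN_ALT) / (k × ULN_AST) = ULN_ALT / ULN_AST,

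which does not depend on k. The document gives neither ULN, so ULN_ALT/ULN_AST is assumed to lie between 0.8 and 1.5.

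| k | ULN ratio 0.8 | ULN ratio 1.0 | ULN ratio 1.5 |
|---|---|---|---|
| 3.5 | 0.8 | 1.0 | 1.5 |
| 4 | 0.8 | 1.0 | 1.5 |
| 8 | 0.8 | 1.0 | 1.5 |
| 10 | 0.8 | 1.0 | 1.5 |

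This needs no value for the missing ULN of the ratio. Whatever that value, patients at k = 0.5 and k = 10 get the same answer: the rule excludes both or neither. To exclude the second, the ratio's ULN would have to lie below 0.8/3 = 0.27 to 1.5/3 = 0.5, and the rule would then also exclude people with normal enzymes. A limit on levels separates the two patients.

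**3. The opposite error**

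With equal enzyme ULNs, ALT at 0.9 × ULN and AST at 0.25 × ULN give 0.9/0.25 = 3.6. Neither enzyme is raised, yet the patient is excluded if the ratio's ULN is taken as anything below 3.6/3 = 1.2.

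**4. What the other items leave uncovered**

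Let DAIDS grade 3 begin at g × ULN. The document does not give g. It is varied here from 3 to 8; the upper end is borrowed from the level-only stopping rule in {11b} as a bound for illustration and is not a DAIDS value. The band that a level rule would exclude, and that both item 6 and the literal item 7 miss, runs from 3 to g × ULN, with width g − 3.

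| g | Width (× ULN) |
|---|---|
| 3 | 0 |
| 4 | 1 |
| 5 | 2 |
| 6 | 3 |
| 8 | 5 |

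This is an upper bound. Item 14 and the bilirubin part of item 7 remove some patients inside the band.

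**The case against.** The strongest reply is that this is an obvious slip. Three times ULN makes sense only for a level, the neighbouring limits confirm that reading, and no site could apply a ratio limit that has no reference value. Sites would read it as ALT or AST, or ask. Nothing in the document shows that any site used a ratio. Safety cover exists elsewhere: items 6 and 14, the bilirubin limit, liver function tests at screening and at every treatment visit (Table 1), and the stopping rules. The uncovered band rests on an assumed cut-off and may have zero width. Trial status expected recruitment to end in early 2024 and the article appeared on 1 April 2024, so a correction would change little screening. The trial runs under protocol version 2.0, which is not shown and may be worded correctly.

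Most of this stands, and it limits the practical weight of the point. It does not make the printed rule right. Dropping the word ratio still leaves open whether either enzyme or both must exceed the limit. The other exclusions cover only part of the range unless DAIDS grade 3 starts at or below 3 × ULN. On-treatment monitoring and stopping rules act after exposure, so they do not replace an entry limit. The unseen version 2.0 is a reason to check it before choosing the remedy.

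**Conclusion.** The concern holds. The enzyme limit in exclusion criterion 7 is wrong as written: it cannot be applied without inventing a ULN for the ratio, and with any such value it cannot detect ALT and AST rising together. It is most likely a wording error, and the document's other hepatic limits show that levels were meant.

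The size is modest. At most, the uncovered group lies between 3 × ULN and the DAIDS grade 3 cut-off: zero width if that cut-off is 3 × ULN, 2 × ULN if it is 5, and 5 × ULN if it is 8, before item 14 is applied. The cut-off and the ratio of the two enzyme ULNs are assumptions. The number of patients affected cannot be derived, and it is zero if sites worked with levels. The point should be corrected because it is a liver-safety eligibility rule and the correction is cheap. Confidence is medium, mainly because the wording of version 2.0 is not visible.

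**What to change.** 1. Compare exclusion criterion 7 with operating protocol version 2.0 and correct whichever document is wrong.
2. Replace the enzyme part with: *ALT or AST level greater than three times the ULN*. The clinical team should confirm the threshold and that either enzyme alone suffices.
3. Only if sites applied the ratio wording, check the screening ALT and AST of randomised participants against the corrected rule.

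**Cost.** If only the article is wrong, a one-line correction. If version 2.0 has the same wording, an amendment is needed; section {25} states: "Protocol amendments must not be implemented without prior approval of the Research Ethics Committee (REC) and/or IRB". The check in step 3 needs no new data: the clinical chemistry panel in Table 1 is done at screening, and its footnote reads "Will include liver and kidney function tests and electrolytes and blood glucose measurement". It would cover at most 212 participants. Sample size, significance level and the primary analysis stay as they are.
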